### Secondary objectives

Compare adults with SCI with and without MCI against a range of psychosocial and secondary health outcomes (e.g., depression, health complications, quality of life).

### Study design

An inception cohort longitudinal study will follow adults with SCI from the first 24–48 h of their presentation to the emergency department. The primary outcome cognition and its predictors and secondary outcomes will be measured across rehabilitation and discharge up to 12-months post-injury.

### Settings

Participants will be recruited from two major acute-care SCI units in New South Wales, Australia; namely, Prince of Wales Hospital and Royal North Shore Hospital from December 2019 through December 2021. Subsequently, they will be followed over the course of their rehabilitation at a specialised rehabilitation centre; i.e., Royal Rehab or Prince of Wales Hospital, until discharge. The 12-month post-injury follow-up assessments will be conducted online when participants are living in the community.

### Participants

#### Inclusion criteria

Aged 17–80 years inclusive with acute SCI from non-traumatic or traumatic etiology;

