**Discussion:**

The prospective design will reveal change in cognitive functioning across time and unveil different outcome trajectories; thus addressing the lack of knowledge on trajectories of MCI and MCI subtypes in SCI. Through subtyping MCI, we hope to yield groups of cognitively impaired individuals with SCI that are potentially more homogenous and thereby stable and predictable. This is the first study to capture emergency department and acute care diagnostic evidence of mild TBI, which has been poorly controlled in previous studies. Our study will also be the first to distinguish the contribution of TBI from other factors to the development of MCI in individuals with SCI.

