## Background

Spinal cord injury (SCI) occurs as the result of damage to the nervous system and spinal cord, associated with bruising or severing in traumatic injuries [1], or to degeneration of the spine, infections, vascular accidents, or cancerous tumours in non-traumatic injuries [2]. SCI is associated with a range of secondary health conditions, including; sleep disturbance [3, 4], psychological disorder [5], chronic pain [6], fatigue [7, 8], and autonomic nervous system dysfunction [9, 10].

Cognitive impairment can be a significant problem following SCI, with a recent systematic review indicating the occurrence of cognitive impairment among individuals with SCI is in the range of 10 and 60% [11]. In line with this, it has been proposed that individuals with SCI demonstrate an accelerated cognitive aging process [12, 13], to the extent that they may be 13 times more susceptible to cognitive impairment when compared to able-bodied individuals [14]. Studies in people with SCI have mostly investigated mild cognitive impairment (MCI), a form of impairment that is defined by subjective impairments that are objectively verified without serious impairments in functioning [15–19], raising questions regarding the clinical significance of cognitive impairment for SCI rehabilitation outcomes.

A number of issues have contributed to confusion regarding the definition and nature of cognitive impairment as it relates to SCI, with varying operationalisations of the construct making it difficult to confirm the severity and hence clinical relevance of cognitive impairment in SCI [11, 14]. These issues which limit understanding of the effects of MCI on outcomes following SCI are discussed below:

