### Participant allocation to groups

Allocation to groups will be based on the absence or presence of cognitive impairment as presented in Fig. 1. Cognitive performance will be assessed using a validated neuropsychological screen. The number of participants will be up to 50 per group, and recruitment will be stratified so that similar numbers of females/males and tetraplegia/paraplegia are allocated to groups. The criteria for a diagnosis of MCI, and hence allocation to cognitively impaired versus not-cognitively impaired groups, will accord with those proposed by Jak et al. [77], requiring scores > 1 standard deviation below normal on ≥2 tests within a cognitive domain on a standardised neuropsychological test. These criteria have been selected as they have demonstrated greater stability over time when compared to alternative conventional criteria as proposed by Petersen, that require scores of > 1.5 standard deviations below normal on a single test within one cognitive domain on neuropsychological testing. We will subtype MCI as follows: *Single Domain Amnestic* if only the memory domain is impaired; *Single Domain Non-Amnestic* if only one non-memory domain is impaired; *Multiple Domain Amnestic* if memory and at least one other domain shows impairment; and *Multiple Domain Non-Amnestic* if there are impairments in more than one non-memory domain [78].

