**Predictors* and secondary outcomes****					
**Measure**	**Measurement tool**				
Autonomic assessment*	HRV		✓	✓	✓
Current medications*	Medical records	✓	✓	✓	✓
Diagnostic evidence of TBI*	Cerebral CT/MRI scan	✓			
	GCS	✓			
	PTA	✓			
Demographics*	Medical records	✓			
Environmental factors*	Carer/family status		✓	✓	✓
	Compensation status		✓	✓	✓
Injury characteristics*	Medical records	✓			
Medical History*	Medical records	✓			
Other co-morbidities	Medical records*	✓			
	SCI SCS**		✓	✓	✓
Participation measure**	WHODAS domain				✓
Personal factors**	ADAPSS		✓	✓	✓
	Brief COPE		✓	✓	✓
	CD-RISC Short Form		✓	✓	✓
	MSES		✓	✓	✓
	WHO ASSIST		✓	✓	✓
Psychological measures**	GAD-7		✓	✓	✓
	PCL-5		✓	✓	✓
	PHQ-9		✓	✓	✓
Psychosocial measures**	Berlin Questionnaire		✓	✓	✓
	FSS		✓	✓	✓
	ISCoS pain dataset		✓	✓	✓
	PCS		✓	✓	✓
	PSQA		✓	✓	✓
	SSQ		✓	✓	✓
QoL measure**	EQ-5D-5L		✓	✓	✓
Return to work**	Questionnaire				✓
Severity of injury*	SCI: AIS and FIM	✓			
	TBI: WPTAS	✓			
Transition ED*	ED record	✓			
Vital signs*	BP, HR, RR, and Temp	✓	✓	✓	✓

*Abbreviations*: *ADAPSS* Appraisal of DisAbility Primary and Secondary Scale, *AIS* American Spinal Injury Association Impairment Scale, *BP* blood pressure, *Brief COPE* Coping Orientation to Problems Experienced, *CD-RISC* Connor-Davidson Resilience Scale, *ED* Emergency Department, *EQ-5D-5L* Euro Quality of Life 5-Dimensional 5-level, *FIM* Functional Impairment Scale, *FSS* Fatigue Severity Scale, *GAD-7* Generalized Anxiety Disorder 7-Item Scale, *GCS* Glasgow Coma Scale, *HR* heart rate, *HRV* heart rate variability, *ISCoS* International Spinal Cord Society, *MH* Mental health, *MSES* Moorong Self-efficacy Scale, *NUCOG* Neuropsychiatry Unit Cognitive Assessment Tool, *PCS* Pain Catastrophizing Scale, *PHQ-9* Patient Health Questionnaire-9, *PSQA* Pittsburgh Sleep Quality Assessment, *PTA* post-traumatic amnesia, *PCL-5* Post-traumatic Stress Disorder Checklist for the Diagnostic and Statistical Manual of Mental Disorders Firth Version, *RR* respiratory rate, *SCI* spinal cord injury, *SCI SCS* Spinal Cord Injury Secondary Condition Scale, *SSQ* Social Support Questionnaire, *TBI* traumatic brain injury, *Temp* temperature, *WHO ASSIST* World Health Organisation Alcohol Smoking and Substance Involvement Screening Test, *WHODAS* World Health Organisation Disability Assessment Scale, *WPTAS* Westmead Post Traumatic Amnesia Scale

*Predictor measure

**Outcome measure

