### Statistical methods

Data analyses will be performed using SPSS v.25. Descriptive statistics will be generated for all relevant primary and secondary outcomes at all time-points. Multiple regression analyses will be used to identify predictors of MCI at discharge and at 12-months post-injury for the total sample and for all subgroup analyses. Latent class mixture modelling will be used to determine trajectories for different domains of cognitive functioning, as well as for selected secondary measures like anxiety, depressive mood and quality of life. Repeated measures linear mixed model analyses will be used to determine differences between the cognitive impairment versus no cognitive impairment groups for secondary outcomes. All analyses will be adjusted for factors suspected to confound results, such as level and completeness of injury, age, and education.

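### Nearly all non-traumatic cases fall in the no-TBI reference group and aetiology is not a named confounder, so the TBI estimate may be confounded with cause of injury

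*Protocol article*

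**What the plan says.** - **Who enters.** Inclusion criteria: "Aged 17–80 years inclusive with acute SCI from non-traumatic or traumatic etiology". The Background attributes the non-traumatic form "to degeneration of the spine, infections, vascular accidents, or cancerous tumours in non-traumatic injuries". Severe TBI is excluded; milder TBI is not.
- **What is claimed about TBI.** Abstract, Discussion: "Our study will also be the first to distinguish the contribution of TBI from other factors to the development of MCI" in people with SCI. The Bias section likewise presents the acute TBI data as the means of telling TBI apart from other predictors. The primary objectives list TBI as one of several example predictors.
- **How TBI is found.** TBI screening relies on indicators around the injury event and during care: coma scale scores, intracranial findings on imaging, post-traumatic amnesia, reported confusion or unconsciousness, and the participant's own account.
- **Who the comparators are.** The last paragraph of the Background describes the controls for TBI as people with SCI without TBI (it also mentions cognitive impairment). It does not limit them to traumatic injury.
- **What is balanced or adjusted.** Participant allocation to groups: "recruitment will be stratified so that similar numbers of females/males and tetraplegia/paraplegia are allocated to groups". Statistical methods: "All analyses will be adjusted for factors suspected to confound results, such as level and completeness of injury, age, and education". The regressions for predictors of MCI are run on the total sample and in subgroups that are not listed.
- **What is collected.** Table 1 marks "Injury characteristics" as a predictor taken from medical records, without itemising it.

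**The concern.** A TBI sustained in the same event as the SCI needs trauma. In a mixed cohort the TBI group is therefore essentially all traumatic, while the no-TBI group blends traumatic cases without TBI and nearly all non-traumatic cases. A TBI coefficient from the total sample then compares traumatic SCI with TBI against that blend. If the two parts of the blend differ in cognition for reasons other than TBI, the difference is credited to TBI, or masks it.

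Such a difference is plausible on the document's own account. Vascular accidents are listed as a cause of non-traumatic SCI, and the article elsewhere names cerebrovascular compromise and age as routes to cognitive impairment. At stake is a result that the study presents as a main novelty.

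**Working it through.** **The plan's own figure.** The only calculated figure, at least 90 participants in Study size, concerns MCI versus non-MCI. It reproduces: controls = (1 + 1/0.6) × φ × (1.96 + 0.84)² / 0.7², where φ is the variance factor for the final timepoint of a three-visit mixed model. With correlation 0.5 and retention of 1, 0.8 and 0.7, this gives 55.8 controls and 33.5 MCI cases, so 56 + 34 = 90. It says nothing about TBI versus no TBI, so the point has to be checked separately.

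**Share of the reference group that is non-traumatic.** Let t be the traumatic share and q the proportion of traumatic cases with TBI. Neither is in the document; both are assumed. Then

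w = P(non-traumatic | no TBI) = (1 − t) / [(1 − t) + t(1 − q)].

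- t = 0.9, q = 0.2: w = 0.10 / (0.10 + 0.72) = 0.12.
- t = 0.5, q = 0.6: w = 0.50 / (0.50 + 0.20) = 0.71.

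**Bias on a cognition score.** Let δ be the difference, in SD units, between non-traumatic SCI and traumatic SCI without TBI that remains after the named adjustments. With aetiology omitted, the size of the bias is δ × w. Over w = 0.12 to 0.71:

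| δ (assumed) | Bias, SD |
|---|---|
| 0 | 0 |
| 0.2 | 0.02 to 0.14 |
| 0.5 | 0.06 to 0.36 |
| 0.8 | 0.10 to 0.57 |

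**Odds ratio for MCI, true TBI effect present.** Assume a true odds ratio of 2.0 within traumatic SCI, 30% MCI in traumatic SCI without TBI, 20–40% of the cohort non-traumatic, and TBI in 30–50% of traumatic cases. Then w runs from 0.20/0.76 = 0.26 to 0.40/0.70 = 0.57. The odds of MCI with TBI are 2.0 × 0.30/0.70 = 0.857 (risk 46%). The reference risk is w × p + (1 − w) × 0.30, where p is the MCI risk in non-traumatic SCI.

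Worked case: p = 0.45, w = 0.57. Reference risk 0.386, odds 0.628, apparent odds ratio 0.857/0.628 = 1.37.

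| p (assumed) | Apparent odds ratio (true 2.0) |
|---|---|
| 20% | 2.27 to 2.67 |
| 30% | 2.0 |
| 45% | 1.37 to 1.67 |
| 55% | 1.08 to 1.49 |

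**Odds ratio for MCI, no true TBI effect.** Assume 40% MCI in traumatic SCI with or without TBI, t from 0.6 to 0.9 and q from 0.2 to 0.6. If non-traumatic risk is 25%, the apparent odds ratio is 1.08 to 1.51. If it is 55%, the range is 0.68 to 0.93.

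All these odds ratios are crude. The planned adjustment for age, level, completeness and education would remove whatever part of the aetiology difference those factors carry.

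**Does an ordinary aetiology covariate suffice?** If no non-traumatic participant has TBI, there are three cells. With mean = b0 + b1 × TBI + b2 × non-traumatic, they are b0 (traumatic, no TBI), b0 + b1 (traumatic, TBI) and b0 + b2 (non-traumatic). Three parameters fit three cells, so b1 is exactly the contrast within traumatic SCI. A three-level factor is the same main-effects model reparametrised. The empty cell rules out only a TBI-by-aetiology interaction.

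**Precision cost.** Take 90 participants, no dropout, two-sided 5% and 80% power. The detectable difference is (1.96 + 0.84) × √(1/n₁ + 1/n₂) SD. Over t = 0.5 to 0.9 and q = 0.2 to 0.6 it is 0.59 to 0.98 SD against all no-TBI cases, and 0.64 to 1.04 SD within traumatic SCI only. Scenario by scenario the rise is 0.01 to 0.12 SD when at least 70% are traumatic. The largest rise is 0.64 to 0.85 SD, at t = 0.5 and q = 0.6.

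**The case against.** The strongest reply is that nothing in the article excludes adjustment for aetiology. The confounder list is introduced as examples, and injury characteristics and medical history are both marked as predictors, so aetiology may well be in the models. The closed covariate list and the coding of TBI usually belong in an analysis plan, which is not shown. The harm is also assumed: the document never says that non-traumatic SCI carries a different cognitive risk from traumatic SCI without TBI, and the odds ratios above are unadjusted.

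Most of this stands, and it rules out several stronger readings that a reader might infer:

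- *That the TBI effect is confounded as planned.* The text supports only that it may be, if aetiology is left out.
- *That an ordinary covariate cannot repair it.* The algebra above shows that it can, for main effects.
- *That no non-traumatic case can be recorded with TBI.* The Background recognises TBI before the SCI, and the confusion or unconsciousness indicator could be met without trauma. The restriction applies to TBI sustained with the injury.
- *That TBI is the primary estimate.* It is one example predictor, and the sample size concerns another comparison.

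The reply does not dispose of the point. The article does fix a mixed cohort, total-sample regressions and a non-TBI comparator not limited to trauma. The five safeguards in the Bias section do not deal with aetiology. Listing a candidate predictor does not define the contrast on which the novelty claim rests.

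**Conclusion.** The point holds as a conditional one. With both aetiologies eligible and the comparator not restricted, nearly all non-traumatic participants sit in the TBI reference group. Leaving aetiology out would let the TBI estimate absorb any difference between traumatic and non-traumatic SCI that remains after adjusting for age, level, completeness and education.

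The bias is zero if no such difference remains and can go either way otherwise. On the assumed ranges it could be negligible (0.02 SD) or substantial (0.57 SD). These figures show what is possible and do not predict this cohort. The change is worth making because it is cheap and protects a claim that the authors stress.

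**What to change.** Add to Statistical methods that the TBI contrast is traumatic SCI with TBI versus traumatic SCI without TBI. It can be estimated in the traumatic participants alone, which also avoids assuming that other covariates act alike in both aetiologies.

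In full-sample models, enter an aetiology indicator alongside TBI. When no non-traumatic case has TBI, a three-level variable (non-traumatic; traumatic without TBI; traumatic with TBI) with traumatic without TBI as reference is equivalent for main effects. Say how an earlier TBI, or a TBI indicator recorded in a non-traumatic case, is classified, because the two codings then differ. Name aetiology among the confounders.

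The cost is about one degree of freedom and some precision: little when most participants are traumatic, more if about half are not. Aetiology is part of the eligibility description and should be in the medical records already being extracted, so no new data should be needed.

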#### Exclusion criteria

Insufficient proficiency in English language;Severe mental (e.g., schizophrenia) and/or physical illness, including severe TBI.

### Participant allocation to groups

Allocation to groups will be based on the absence or presence of cognitive impairment as presented in Fig. 1. Cognitive performance will be assessed using a validated neuropsychological screen. The number of participants will be up to 50 per group, and recruitment will be stratified so that similar numbers of females/males and tetraplegia/paraplegia are allocated to groups. The criteria for a diagnosis of MCI, and hence allocation to cognitively impaired versus not-cognitively impaired groups, will accord with those proposed by Jak et al. [77], requiring scores > 1 standard deviation below normal on ≥2 tests within a cognitive domain on a standardised neuropsychological test. These criteria have been selected as they have demonstrated greater stability over time when compared to alternative conventional criteria as proposed by Petersen, that require scores of > 1.5 standard deviations below normal on a single test within one cognitive domain on neuropsychological testing. We will subtype MCI as follows: *Single Domain Amnestic* if only the memory domain is impaired; *Single Domain Non-Amnestic* if only one non-memory domain is impaired; *Multiple Domain Amnestic* if memory and at least one other domain shows impairment; and *Multiple Domain Non-Amnestic* if there are impairments in more than one non-memory domain [78].

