## Methods

### Primary objectives

Determine the rate of MCI in adults with SCI, including MCI sub-types: single domain amnestic, multiple domain amnestic, single domain non-amnestic, and multiple domain non-amnestic;Identify predictors of MCI (e.g., mood disturbance, polypharmacy, presence of TBI) and moderators of relationships between predictors and MCI (e.g., education, estimated premorbid intelligence, practice effects);Investigate how predictors operate over time to influence manifestations and trajectories of MCI (e.g., how depression and/or polypharmacy affect MCI).

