### Study size

Our preliminary study of 150 adults with SCI [14] found a 10-point difference in the NUCOzG total mean scores (with a SD of 6.3) between the participants with MCI (*n* = 60) versus those without (*n* = 90). Therefore, the resultant effect size was large being > 1.5. For this prospective study, to test the primary outcome of interest, we are conservatively assuming a between-groups moderate Cohen’s d effect size of 0.7, a group allocation of 0.6:1 MCI: non-MCI, an alpha of 0.05, 80% statistical power, three assessment points, a compound symmetry correlation matrix (rho = 0.5), and attrition rates of 20 and 30% between assessment points. The estimated required overall sample size is at least 90 participants. This calculation was based on linear mixed model of repeated measures with a general correlation structure and the estimated sample size includes limited interaction effects [99].

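### Capping each MCI-status group at 50 samples on the outcome whose rate is the first primary objective, and cannot be squared with at least 90 participants at 0.6:1

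*Protocol article*

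**What the plan says.** Primary objectives: the first is to "Determine the rate of MCI in adults with SCI, including MCI sub-types". The second begins "Identify predictors of MCI (e.g., mood disturbance, polypharmacy, presence of TBI", and then turns to moderators.

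Participant allocation to groups: "Allocation to groups will be based on the absence or presence of cognitive impairment". The size and make-up of each group are then limited: "up to 50 per group, and recruitment will be stratified so that similar numbers of females/males and tetraplegia/paraplegia are allocated to groups".

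Study size: the calculation assumes "a group allocation of 0.6:1 MCI: non-MCI" and arrives at a minimum of 90 participants. It cites a preliminary study of 150 people, 60 of them with MCI. The Abstract plans for about 100.

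Variables, Table 1: cognition (NUCOG) is first measured at the rehabilitation visit (V1). Demographics and injury characteristics are starred as predictor classes.

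Statistical methods: predictors of MCI are examined by regression at discharge and at 12 months. Level of injury is listed among the factors to adjust for.

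**The concern.** A rate can be read directly from a cohort only if entry does not depend on the condition being counted. Here the design is called an inception cohort, but the number with and without MCI is limited by MCI status itself. Once one group is full, further people of that status are either left out or the cap is ignored, and the article does not say which. It gives neither a denominator for the rate nor a weighting back to the source population. A primary estimate could therefore reflect the recruitment rule rather than the population.

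The cap, the ratio and the sample size also cannot all be followed, so staff running the study must break one of them.

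The balancing sentence raises a second, conditional problem. If sex and tetraplegia/paraplegia are made alike in the MCI and non-MCI groups, their association with MCI at baseline is set by recruitment, and later covariate adjustment cannot restore it.

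**Working it through.** **1. The plan's own sample size.** Inputs from Study size: d = 0.7, alpha 0.05 (taken as two-sided), power 80%, ratio 0.6:1, three visits, compound symmetry with rho = 0.5, attrition 20% and 30% (read as cumulative retention of 1, 0.8 and 0.7).

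- MCI share: 0.6/1.6 = 0.375.
- One visit, no attrition: N = (1.960 + 0.842)² / 0.7² × (1/0.375 + 1/0.625) = 16.02 × 4.267 = 68.3, or 43 + 26 = 69 after rounding up by group.
- Mixed model, group difference at the last visit, with that dropout: the variance rises by a factor of about 1.307, so N = 68.3 × 1.307 = 89.3, or 56 non-MCI + 34 MCI = 90.

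The stated 90 is reproduced. Reading the attrition as 20% and then 30% of those remaining gives 104 to 106 instead, which would make the conflict below larger.

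**2. Cap against ratio and size.** The non-MCI number is N/1.6.

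| N | MCI | non-MCI | within 50? |
|---|---|---|---|
| 80 | 30 | 50 | yes, just |
| 90 | 33.75 | 56.25 | no |
| 100 | 37.5 | 62.5 | no |

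**3. MCI share that the cap allows.** With at most 50 in each group, the MCI count lies between N − 50 and 50.

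| N | MCI count | MCI share |
|---|---|---|
| 80 | 30 to 50 | 37.5% to 62.5% |
| 90 | 40 to 50 | 44.4% to 55.6% |
| 95 | 45 to 50 | 47.4% to 52.6% |
| 100 | 50 | 50% |

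The planned 37.5% and the preliminary 60/150 = 40% both fall outside the range at 90 and at 100. Under a binomial count, 90 consecutive participants would break a cap with probability about 89% if the true rate is 37.5%, and about 78% if it is 40%.

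**4. Size of the error if both groups are filled, true rate 37.5%.**

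- The non-MCI group is full after 50/0.625 = 80 people assessed, 30 of them with MCI.
- Reaching 50 with MCI takes 50/0.375 = 133 assessed, about 83 of them without MCI, so about 33 are surplus.
- The rate in the retained sample is 50/100 = 50%, which is 12.5 points too high. If those with MCI are kept without selection, each subtype rate is inflated by the same factor, 50/37.5 = 1.33.
- The rate in everyone assessed is 50/133 = 37.5%. The error disappears if the surplus is counted.

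**5. Balancing, on the reading that composition is equalised across MCI groups.** Illustrative assumption, not from the documents: baseline MCI in 50% of people with tetraplegia and 30% with paraplegia.

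- True baseline odds ratio: (0.5/0.5)/(0.3/0.7) = 2.33. With identical composition in both groups it becomes 1.0.
- For 12 months, assume 70% of baseline MCI persists, 10% of the others develop it, and injury level has no direct effect on change. Tetraplegia: 0.5 × 0.7 + 0.5 × 0.1 = 0.40. Paraplegia: 0.3 × 0.7 + 0.7 × 0.1 = 0.28. Odds ratio (0.40/0.60)/(0.28/0.72) = 1.71.
- Over persistence of 60% to 80% and onset of 10% to 15%, the odds ratio is about 1.5 to 1.8. With balancing it falls to 1.0, because all of it is carried by baseline status. Any direct effect on onset or recovery would remain.

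**6. Power.** At 30 + 50 = 80 the power is about 75.5%. A 1:1 split needs 16.02 × 4 × 1.307 = 83.7, or about 84. The cap is therefore a problem for the rate and the predictors, and not for a comparison of two filled groups.

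**The case against.** The best defence is that the wording sets a ceiling, not a target. Nothing says that recruitment continues until both groups hold 50. Assigning people to groups may be no more than classification by test result, and a rate could be taken from everyone screened, a detail that an article may leave to the full protocol. This stands in part. A reader might infer that the design fixes the rate at 50% whatever the truth. The documents do not support that: the share is fixed only at N = 100, is confined to a range at N = 90, and the 12.5-point error needs both continued filling and uncounted exclusions. The ceiling reading does not rescue the plan, however, because the stated ratio and minimum size break the ceiling by themselves.

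A reader might also infer that sex and injury level are erased as predictors. That is too strong, for four reasons.

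- Neither is among the example predictors in the objectives. They fall only within broad starred classes in Table 1, and injury level is named as an adjustment factor.
- The regressions are at discharge and 12 months, where effects on new onset or recovery remain estimable.
- The sentence asks for similarity, not exact matching. It could also mean recruiting comparable numbers of each sex and injury category overall, which would not force a null. Fig. 1, which sets out the allocation, was not available for this review.
- The Background's argument about injury above T6 does not carry over. That contrast is not tetraplegia against paraplegia, the same section describes a cardiovascular route in paraplegia, and the mechanism is to be measured by heart rate variability, blood pressure and heart rate, none of which is balanced.

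**Conclusion.** The point holds in two parts of different strength.

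Firm, from the documents alone: the 50-per-group cap, the 0.6:1 ratio and the minimum of 90 are incompatible (56 against 50; compatible only to N = 80), and the cap conditions sampling on the outcome of the first primary objective. Applied to an analysed sample of 90 to 100, it excludes the rate that the plan itself assumes. At a true 37.5% the overstatement reaches 12.5 points if both groups are filled and the surplus is not counted.

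Conditional: if the balancing equalises sex and injury level across MCI groups, their marginal association with baseline MCI is pushed towards null and their associations at discharge and 12 months are attenuated. How far depends on persistence and onset, which the documents do not give.

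This is more than missing detail, because following the stated cap at the stated size would bias a primary estimate, and analysis cannot repair that unless those left out are recorded.

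**What to change.** Delete the 50-per-group cap and the balancing of sex and tetraplegia/paraplegia across MCI groups. Enrol eligible consenting patients consecutively to about 100. Estimate the MCI rate and the subtype rates in everyone assessed with the NUCOG at V1. Include sex and injury level as covariates.

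If any quota is kept: log everyone assessed, compute the rates from that full denominator, weight the retained sample by the inverse of the sampling fraction, and state that baseline associations of sex and injury level with MCI are not estimable.

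The cost is a change of wording and simpler recruitment. Groups will be unequal, about 37:63 at N = 100, which Study size already assumes. At N = 90 and a rate of 37.5%, the 95% interval is 37.5% ± 1.96 × √(0.375 × 0.625/90), or about 27.5% to 47.5%: wide, but an interval for the rate in the population recruited.
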